### 1) Online self-help program with individual support (IND):

The caregiver can now use the online self-help program for four weeks. He/she receives additional messages from psychologist three times per week, to give additional information about the modules (e.g. using examples), clarify individual content-related questions and strength the motivation of the caregivers in dealing with individual obstacles. The caregiver can contact the psychologist by writing messages in the same secure system.

## **2) Online self-help program with automated support (AUT):**

The caregiver can now use the online self-help program for four weeks. He/she receives additional fully automated messages included regular motivational e-mails, reminders with encouraging messages, and feedback on completed modules. The caregiver cannot reply to the automated messages sent by the online program.

## **3) treatment as usual control condition with written information (TAU):**

The caregiver gets access to the patient information „Depression – Angehörige und Freunde“, which is developed by the ÄZQ based on patient guidelines of unipolar depression. After the study period of three month the caregivers of the TAU-control-condition can also use the online self-help program with automated support.

One week after randomization (T1) the caregiver will be asked to fill in a short questionnaire concerning the psychological distress of the caregivers (K-10). After the intervention period of four weeks, the caregivers and depressed persons fill in the psychological questionnaires again (T2). At this time, there will be additional questionnaire for the caregivers who were randomized to one of the active interventions, asking for the acceptance, adherence to and usage of the online program. All caregivers are also asked, if adverse events occurred during the intervention period. Three months after T0 (T3) the caregivers and depressed persons will fill in the psychological questionnaires again und the caregivers will be asked for occurred adverse events in the last 8 weeks.

At T2 and optionally T3, individual participants (caregivers and depressed persons) will be selected based on stratification criteria and invited to take part in a research interview of approximately 60-90 minutes by telephone. The participation in the interview is voluntary and does not affect the general study participation in any way. If the participants are interested in taking part, they will be given an additional study information and consent form for the interview.

The participant's timeline is shown in the following figure:

[figure not shown]

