## 4.6 Sample Size

The numbers of caregivers to be randomized to the respective intervention and control groups IND:AUT:TAU are  $n=500:500:250$ . This accounts for an expected 20% rate of missing K-10 outcome measurements at T2 – yielding an expected  $n=400:400:200$  non-missing primary outcomes – and for the following power considerations. Randomized groups will be compared using a sequential closed test procedure: To guarantee a multiple significance level of 5%, confirmatory statistical testing at nominal significance level  $\alpha=5\%$  will continue until the first non-significant result. Pairwise comparisons between randomized groups will be performed via calculation of a two-sided 95% confidence interval for the difference of means, for which exclusion of a zero difference is equivalent to rejection of the null hypothesis in an unpaired t-test of equal means at two-sided significance level  $\alpha=5\%$ . The first and second statistical test to reject equalities  $IND=TAU$  and  $AUT=TAU$  of mean pre-to-

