### 6.1.2 Psychological variables

The psychological variables will be collected by the following questionnaires (or interview), which the caregivers fill in (or participate in) at T0, T1 (only K-10), T2 and T3:

|                                                                  | Screening | T0 | T1 | T2  | T3  |
|------------------------------------------------------------------|-----------|----|----|-----|-----|
| Caregiver                                                 |           |    |    |     |     |
| informed consent                                                 | x         |    |    |     |     |
| Screening – questions concerning in- and exclusion criteria      | x         |    |    |     |     |
| sociodemographic data and relationship with the depressed person |           | x  |    |     |     |
| internet literacy                                                |           | x  |    |     |     |
| K-10                                                             |           | x  | x  | x   | x   |
| IEQ-EU                                                           |           | x  |    | x   | x   |
| SCL-K-9                                                          |           | x  |    | x   | x   |
| D-Lit                                                            |           | x  |    | x   | x   |
| FFB                                                              |           | x  |    | x   | x   |
| WHO-5                                                            |           | x  |    | x   | x   |
| acceptance, adherence and usages questionnaire                   |           |    |    | x   |     |
| adverse events questionnaire                                     |           |    |    | x   | x   |
| Qualitative interview                                            |           |    |    | (x) | (x) |
| depressed person (if applicable)                          |           |    |    |     |     |
| informed consent                                                 | x         |    |    |     |     |
| PHQ-9                                                            |           | x  |    | x   | x   |
| Qualitative interview                                            |           |    |    | (x) | (x) |

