#### **6.3.5 Analysis of secondary outcomes**

Secondary outcomes at T2, four weeks after randomization, and T3, three months after randomization, will be evaluated in a linear mixed model per outcome scale, with a compound symmetry covariance matrix to account for correlation between T2- and T3-outcomes of the same caregiver or depressed person. Independent variables will be those of the main primary analysis, plus time point (T2, T3). The details will be fixed in the statistical analysis plan.

Subgroup analyses, moderator and mediator analyses will be performed as described for the primary outcome above.

Furthermore, the results seen in the Facing Depression Together trial will be compared to historical controls of face-to-face psychoeducation groups for caregivers of depressive in-patients from the multicentre SCHILD study (Frank, Wilk, et al., 2015).

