### **7.2 Harms**

The objective of this online-coach is to effect a positive change of caregivers' psychological burden and everyday life. Each change includes a risk for undesirable side effects. Side effects can be impacts on everyday life, interpersonal relationships (e.g. conflicts due to caregivers setting more boundaries towards the patients) and increased awareness of the burdens. Moreover, a temporary burden through the active analysis of actual stress factors is possible. For risk assessment (serious) adverse events ((S)AE) will be defined ahead of the study and recorded during the course of

studies. (Serious) adverse events are the occurrence or deterioration of psychiatric symptoms of the caregiver or the depressive person.

In case of a (S)AE there is an emergency button on the website of the online program, where the participant can find information and contacts of emergencies services and will be asked to contact them.

If (S)AE occur in the psychological message system contact or if participants contact a study member in case of an (S)AE, the lead investigator will be informed of the (S)AE immediately and will decide on the further procedure (e.g. study exclusion and outpatient or inpatient treatment recommendations).

For the following reasons, the intervention will be ceased in subjects of the study:

- Revocation of the subject's declaration of consent
- If, in the opinion of the lead investigator, further participation in the study would have harmful effects on the subject or the depressive person
- In case of new exclusion criteria
- If the emotional burden for the subject is too serious to cope with it himself, and intensive (professional) support is needed

Exclusion is decided by the lead investigators, in case of fulfilling one of the mentioned criteria. The reason for exclusion will be recorded. If needed, excluded subjects will be supported in searching further consulting or treatment. Also, if the subject revokes the informed consent, the subsequent reason will be recorded.

The lead investigator will monitor the progress of the study with regard to safety-relevant development. The lead investigator will discontinue the study, if:

- the cost-benefit ratio for the caregiver or the depressive ill person changes significantly
- there are indications, that the security of the caregiver or the depressive ill person is no longer guaranteed
- the continuation of the study is no longer justified by ethical or medical reasons

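### For caregivers who miss T2 but answer T3, no answered adverse-event questionnaire covers the intervention period, and the T2 and T3 recall windows may not join

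*Protocol*

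**What the plan says.** Section 4.5 describes two adverse-event questions. At T2: "All caregivers are also asked, if adverse events occurred during the intervention period". At T3: "the caregivers will be asked for occurred adverse events in the last 8 weeks". Section 6.1.1 repeats the 8-week look-back. The schedule in section 6.1.2 lists the "adverse events questionnaire" at T2 and T3 and not at T1. Nothing changes the T3 question for a caregiver who did not answer T2.

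The timing of T3 is given only in months. Section 4.5 has "Three months after T0 (T3) the caregivers and depressed persons will fill in the psychological questionnaires again", and section 6.3.5 has "Secondary outcomes at T2, four weeks after randomization, and T3, three months after randomization".

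Section 4.6 plans for an "expected 20% rate of missing K-10 outcome measurements at T2". Section 6.1.4 provides repeated reminders at T1, T2 and T3 and asks people who stop the intervention to complete all measurements.

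Section 7.2 adds a spontaneous route: "If (S)AE occur in the psychological message system contact or if participants contact a study member", the lead investigator is informed.

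**The concern.** The two questions should together cover the follow-up of anyone who keeps answering. They are worded so that this depends on T2 being answered. The T3 question has a fixed length and does not reach back into the intervention, so a caregiver who returns at T3 after missing T2 is reachable but is not asked about the weeks when the program was delivered. Even for someone who answers both, a fixed 8 weeks may fall short of the interval between T2 and T3.

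Section 7.2 defines adverse events as new or worsening psychiatric symptoms in the caregiver or the depressed person, and it expects possible conflicts and temporary burden from working through the material. The intervention weeks are thus where harms data matter most. The spontaneous route is also uneven. IND caregivers exchange messages with a psychologist (section 4.5), AUT caregivers cannot reply to theirs, and TAU has no message support. Events missed by the questionnaire can therefore surface more easily in IND, which would distort a comparison of arms.

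**Working it through.** **Inputs.** T2 is day 28 (four weeks after randomisation, section 6.3.5). The T3 look-back is 8 weeks = 56 days (sections 4.5 and 6.1.1). T3 is three months, which is 84 days if a month is taken as four weeks and 89 to 92 days as calendar months. T0 and randomisation are treated as the same day, since randomisation follows completion of the T0 questionnaires.

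**The plan's own figures.** 400/0.80 = 500 and 200/0.80 = 250, so the randomised numbers 500:500:250 agree with 20% missing. The 8-week look-back joins the T2 question only if T3 is day 84: 84 − 28 = 56 days.

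**Formulas.**
- Days between the windows, T2 answered and T3 on time: (T3 − 28) − 56.
- Start of the T3 window: T3 − 56.
- Intervention days inside the T3 window: max(0, 28 − (T3 − 56)).
- Share of follow-up with no answered question if T2 is missed: (T3 − 56)/T3.

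| T3 (days) | T2 to T3 (days) | Days between windows | Share of follow-up | T3 window starts | Intervention days covered by T3 | Share not covered if T2 missed |
|---|---|---|---|---|---|---|
| 84 (12 weeks) | 56 | 0 | 0% | week 4.0 | 0 of 28 | 33.3% |
| 89 | 61 | 5 | 5.6% | week 4.7 | 0 of 28 | 37.1% |
| 91 (13 weeks) | 63 | 7 | 7.7% | week 5.0 | 0 of 28 | 38.5% |
| 92 | 64 | 8 | 8.7% | week 5.1 | 0 of 28 | 39.1% |

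Each day by which T3 is answered late moves the window forward by a day and adds a day to the gap. A late T2 does not shorten the gap on the literal wording, because the T2 question is tied to the intervention period and not to the day of completion.

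**How many caregivers.** If the 20% applies to the whole T2 assessment, 0.20 × 500 = 100, 0.20 × 500 = 100 and 0.20 × 250 = 50, in total 250 of 1250. A reworded T3 item can recover only those who then answer T3. With f the share who do, that is 250 × f: 0 if f = 0, 125 if f = 0.5, 250 if f = 1. The protocol gives no value for f.

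**The case against.** The strongest reply is that the protocol's figures fit together: four weeks plus 8 weeks is 12 weeks, which is one way to read three months, and then nothing is lost between the windows. The timeline figure in section 4.5, which was not available, may settle this. The protocol also describes the question in prose, so the final item wording is not established. This stands as far as the gap between the windows is concerned, and the range must include zero. It does not help a caregiver who missed T2: at 12 weeks the T3 window still covers none of the intervention.

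Three stronger statements are tempting, and the protocol does not support them.

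- *T2 non-responders are never asked.* They are sent the T2 questionnaire and reminded repeatedly (section 6.1.4). What is true is that no answered questionnaire covers the period.
- *AUT and TAU have no way to report.* Section 7.2 accepts contact with a study member without restriction by arm, and section 8.1 offers a telephone contact throughout the study. Only the psychologist-message route is confined to IND.
- *The questionnaire is the only safety data.* K-10 is measured at T0, T1, T2 and T3, SCL-K-9 and WHO-5 at T0, T2 and T3, and reasons for withdrawal or exclusion are recorded. The T1 K-10 can show early worsening even if T2 is missed. It is a partial substitute: with a 30-day recall answered one week after randomisation, about 7 of its 30 days fall in the intervention, and it concerns the caregiver only.

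It is also fair that a longer recall for T2 non-responders makes recall unequal, and more so if T2 non-response differs by arm. This is a real but minor cost, because the alternative for these caregivers is no answer at all, and results can be shown by recall period. Finally, adverse events lie outside confirmatory testing and the protocol expects low risk. That limits the weight of the point but does not remove it.

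**Conclusion.** The point holds in this form. On every reading of three months, questionnaire-based adverse-event collection covers 0 of the 28 intervention days for caregivers who miss T2 but answer T3. The number affected is at most 250 of 1250 (100:100:50). This assumes that the 20% planned for missing K-10 applies to the whole T2 assessment and that all of these caregivers answer T3; the true number may be much smaller. Those who stop responding altogether are not helped by any T3 wording.

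The gap between the windows is the lesser part: 0 days if T3 is at 12 weeks, 5 to 8 days on calendar months, and more if T3 is answered late.

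A reader might infer that harms will be under-recorded, or that the arms will differ in recorded harms. The protocol gives no event rates and no T3 response among T2 non-responders, so both are risks of unknown size. The primary analysis is not touched.

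**What to change.** 1. State the timing of T3 in weeks, and use the same anchor (T0 or randomisation) in sections 4.5, 6.1.1 and 6.3.5.
2. Word the T3 item as *since your last completed adverse-event questionnaire, or since the start of the study if you have not completed one*. The platform can select the version from its own record of T2.
3. Have the T2 item ask up to the day of completion, so that the two windows join whatever the delay.
4. Report questionnaire-collected events by arm, and list events detected through the IND messages separately. This can be written into the SAP.

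The cost is two item texts and one platform branch. Recall becomes longer for those who missed T2 (about 12 to 13 weeks instead of 8 to 9) and unequal between caregivers, so the report should flag the recall period. The change is cheap before data collection; the missing answers cannot be reliably recovered afterwards.

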## 4.6 Sample Size

The numbers of caregivers to be randomized to the respective intervention and control groups IND:AUT:TAU are  $n=500:500:250$ . This accounts for an expected 20% rate of missing K-10 outcome measurements at T2 – yielding an expected  $n=400:400:200$  non-missing primary outcomes – and for the following power considerations. Randomized groups will be compared using a sequential closed test procedure: To guarantee a multiple significance level of 5%, confirmatory statistical testing at nominal significance level  $\alpha=5\%$  will continue until the first non-significant result. Pairwise comparisons between randomized groups will be performed via calculation of a two-sided 95% confidence interval for the difference of means, for which exclusion of a zero difference is equivalent to rejection of the null hypothesis in an unpaired t-test of equal means at two-sided significance level  $\alpha=5\%$ . The first and second statistical test to reject equalities  $IND=TAU$  and  $AUT=TAU$  of mean pre-to-

post-(T2-T0) K-10 changes at significance level  $\alpha=5\%$  will implement the primary objective by comparing online self-help program interventions with control; they have a power of  $1-\beta\approx 99\%$  given a medium effect size (Cohen's  $d$ ) of  $d=0.5$ , and of  $1-\beta=93\%$  if  $d=0.3$ . Such effect sizes appear to be realistic based on a single-arm pre-post comparison following a psychoeducation program which yielded  $d=1.1$  for a shorter version of the primary outcome scale, the K-6 scale (Katsuki et al., 2011). As regards the third comparison among the two online self-help program intervention groups IND and AUT, both superiority of IND over AUT and, to a lesser degree, equality of IND and AUT can appear realistic; it would be worth-while to reject equality  $IND=AUT$  or inferiority of AUT. The pairwise test comparing the two online self-help program intervention groups to reject  $IND=AUT$  has a power of  $1-\beta=81\%$ , given a small effect size of  $d=0.2$ . Confirmatory testing will stop after this comparison. Given equal means  $IND=AUT$  ( $d=0$ ), it would also be of interest to reject inferiority of AUT ( $d=-0.1$ ), i.e. to demonstrate non-inferiority of the less costly intervention AUT compared to the more costly intervention IND at one-sided significance level  $\alpha=2.5\%$ . The power to achieve this secondary objective, i.e. to reject such a small inferiority, is  $1-\beta=29\%$ . Higher recruitment targets to achieve greater power were dismissed for reasons of feasibility. The scenarios considered are summarized in terms of standardized group means shifted towards 0 for the TAU group in the table below (nQuery V8.3.1.0, module MGT0U).

| Standardised mean
IND,AUT,TAU | Power to reject a single null hypothesis (n=400:400:200): |         |         |             |
|----------------------------------|-----------------------------------------------------------|---------|---------|-------------|
|                                  | IND=TAU                                                   | AUT=TAU | IND=AUT | AUT inf IND |
| 0.5, 0.3, 0                      | 99%                                                       | 93%     | 81%     | <1%         |
| 0.5, 0.5, 0                      | 99%                                                       | 99%     | 5%      | 29%         |
| 0.3, 0.3, 0                      | 93%                                                       | 93%     | 5%      | 29%         |

Notes: inf refers to the null hypothesis that AUT is inferior to IND ( $d=-0.1$ ).

## 4.7 Recruitment

Caregivers of depressed persons will be recruited online throughout Germany. As the majority of depressed persons are treated by general practitioners (Gerste & Roick, 2014), general practitioner practices as well as specialist practices for psychiatry and psychotherapy and psychotherapists will be informed and sensitized to the role of caregivers in the treatment of depression. Clinics for psychiatry and psychotherapy will be included in the recruitment strategy as well, because within in-patient care only the

minority of caregivers is able to access psychoeducative offers, so most caregivers are unprepared for the critical phase after the discharge of the depressed patient. We will provide informational material for patients and care-givers (posters, flyers) to interested practices and clinics. Other caregivers will be addressed through online forums, self-help groups for caregivers, self-help contact bureaus, crisis intervention centers and caregivers' associations. Furthermore, information on study participation will be disseminated through 85 regional alliances against depression (Bündnisse gegen Depression) and a patient congress (most recently in Leipzig with more than 1300 participants, half of which caregivers of depressed persons), both organized by the German Depression Assistance Foundation (Stiftung Deutsche Depressionshilfe), as well as through a dedicated informational web page for relatives of depressed persons by the German Depression Assistance Foundation which has several hundred visitors each day. The general public will be addressed through the members' magazines and internet pages of the cooperating health insurance AOK and via advertisements in search engines, social platforms and other media.

The informed consent, delivery of the intervention and data collection will take place on a research platform website set up for these purposes. No information on participants will be processed or communicated during recruitment. Rather, potential participants will be referred to the research website for information and registration.

It is expected that during the twenty-two-month recruiting period about 1600 caregivers will be declared about the study and screened in terms of the inclusion criteria and that 1250 caregivers can be included and randomized within the study.

## **5 Methods: Assignment of interventions**

### **5.1 Allocation**

#### **5.1.1 Sequence generation**

For allocation to the intervention and control groups IND, AUT and TAU, a computer-generated random list with a 2:2:1 ratio is used, with stratification based on the participating caregivers characteristics as follows:

- age (years, 18-40, 41-65,  $\geq 66$ )
- gender (female, male, diverse)
- relation with depressed person (parent, child, partner, other)
- K-10-scale (10-22, 23-50).

These characteristics were selected because each variable could plausibly influence participants' response to the interventions. The K-10 cut-off value was chosen based on its ability to differentiate healthy persons from persons at risk of a mental disorder in the German validation study (Giesinger, Rumpold, & Schüßler, 2008). Details of the randomization algorithm will be documented separately and will not be disclosed to the participants.

